### Demographic and clinical information and further variables

Physicians will be asked to supply details regarding their age, sex, level of occupational qualification, and number of years of experience with cancer patients. Furthermore, they will be asked to answer a questionnaire about the cancer treatment of each of the patients included in the study (current diagnosis, time since diagnosis, status of diagnosis, present and planned cancer treatment, intention of cancer treatment).

Patients will be asked about their past use of CIM and about the empathy of their physicians [24].

### Quantitative data collection

All physicians will be asked to answer questionnaires at several time points. First, by using a web-based survey prior to the e-learning, oncology physicians will provide their baseline information. Second, the physicians will complete a paper-pencil questionnaire after each communication with/handout of the information leaflet to 10 of their patients. Third, each physician will answer a paper-pencil questionnaire after completing the intervention with all 10 patients. Furthermore, physicians will be asked to evaluate the blended learning and to provide medical information about each patient after including them in the study. Patients will complete paper-pencil questionnaires at baseline (prior to the consultation/handout of the information leaflet) and 2 weeks after the consultation/handout of the information leaflet. For the physician-patient-interaction level, a systematic external rating by two independent raters will be conducted during the on-site skills-training workshop. For this, a consultation with a standardized patient will be conducted.

In the case of no or little recruitment, the study team will contact the physicians to offer information and support on how to improve recruitment or how to integrate the consultation into daily routine.

A Standard Protocol Items: Recommendations for Interventional Trials (SPIRIT) Figure and Checklist for this study protocol are provided in Fig. 2 and Additional file 1, respectively.

**Fig. 2 Fig2:**
[figure not shown]
Content of the KOKON-KTO schedule of enrollment, interventions, and assessments according to the Standard Protocol Items: Recommendations for Interventional Trials (SPIRIT) Statement. *Oncology physicians (MD, medical doctor), **Patients

### Data management, storage and security

The data will be managed according to the Standard Operating Procedures (SOPs) and the quality management protocol of the coordinating center (Institute for Social Medicine, Epidemiology, and Health Economics, certified according to DIN EN ISO 9001:2015). An identification number (ID), not containing aspects that allow identification (e.g., initials or date of birth) will be assigned to each study participant (medical doctors (MDs) and patients). Data collection, data entry and data processing will be based on this ID. The data from the paper questionnaires will be entered in this pseudonymized form into a database programmed by a data manager of the Institute for Social Medicine, Epidemiology and Health Economics of the Charité – Universitätsmedizin Berlin. All data will be stored for at least 10 years. The archiving will be pseudonymized. The data will be collected using SoSci-Survey software and written questionnaires. In e-Learning (Moodlerooms), questions will also be asked in order to ascertain the development of the participants’ level of knowledge and experience. Within the scope of the study, only anonymized data will be evaluated. The data from the online survey will be transferred as CSV files and stored in a database at the coordinating center. The telephone interviews will be recorded with a digital sound-recording device, transcribed anonymously and stored using the ID.

### Statistics

All statistical analyses will be considered exploratory. Suitable summary statistics and graphical methods will be used to describe characteristics of the sample at baseline. Mean values and standard deviations (median and percentiles, if applicable) will be calculated for metric variables, frequencies and percentages for categorical variables.

Differences in the outcomes between the two treatment groups will be analyzed by multilevel models (analysis of covariance (ANCOVA) type or logistic-regression-type model). Models will include the physician as a random (clustering) effect, the stratification variables including type of center (hospital department or private practice) and specialization (gynecology or other oncology) as fixed effects, and the respective baseline value (if available) as a covariate. The multilevel structure of the data is due to patients treated within a physician, and physicians working within a cluster. However, due to the small number of physicians per cluster (one to two), the cluster (center) will not be taken into the model. For the treatment effect, adjusted mean values with 95% confidence intervals will be reported. In addition, a blinded analysis of baseline data will be performed to determine relevant baseline differences between the intervention and control groups. For sensitivity analysis, we will repeat the aforementioned models with adjustment for these variables. Furthermore, whether a different intensity of e-learning use (e.g., different increases in knowledge, duration of use) affects the outcomes (“dose-response relationship”) will be investigated. All *P* values will be considered explorative. A detailed statistical analysis plan (SAP) will be developed prior to any data analysis. Data analysis will be performed in SAS Version 9.4 or higher (SAS Inc., Cary, NC, USA) or SPSS Version 23 or higher.

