**Methods/design:**

Forty-eight oncology physicians will be included into a cluster-randomized trial to either participate or not in the blended-learning training. Physicians will then advise 10 cancer patients each, resulting in 480 patients participating in the trial. The blended learning consists of nine units of up to 45 min of e-learning and 18 units of up to 45 min of on-site skills-training workshop focusing. Outcomes will be measured on the physician, patient, and physician-patient-interaction level.

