### Physician recruitment and eligibility

The oncology physicians participating in the KOKON-KTO study will be recruited from hospital departments treating cancer patients (e.g., breast centers, departments for gynecology, ear, nose, throat departments, etc.) and private practices. Oncology physicians in private practices are part of the German health care insurance system and treat patients who are statutorily and privately insured. The described recruitment sites are hereinafter referred to as “hospital departments” and “private practices.”

From each hospital department two oncologists will have to be eligible and will be counted as a cluster. The 48 oncology physicians (24 working with specialization on gynecologic oncology) will be recruited from hospital departments (50%) and private practices (50%).

To allow heterogeneity, half of the participating oncology physicians will have a focus in gynecological oncology, while the other half will have focuses in other cancer entities. In Germany, gynecology is one of the surgical specialties of medicine. However, gynecology also includes a wide range of conservative treatment methods, such as hormone therapy, counseling, contraception methods, and reproductive health. All physicians with a specialization in gynecology participating in this study will have to work with cancer patients on a regular basis in hospital departments or private practices.

Recruitment will take place in the following federal states in Germany: Baden-Württemberg, Bavaria, Berlin, Hamburg, and North Rhine-Westphalia. Heads of hospital departments as well as representatives of private practices will be contacted by letters. The heads of hospital departments will be invited to send two oncology physicians each and the representatives of private practices will be invited directly to participate. Oncology physicians will be screened for their eligibility after receiving the study documents and subsequently will be included in the study on a “first-come first-served” basis.

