### Random allocation procedures

The cluster-randomization into both groups will occur on a hospital department or private practice level. Whereas each private practice will provide only one oncology physician (cluster 1), hospital departments will each provide two oncology physicians (cluster 2). Randomization of clusters will be stratified by type of center (hospital department or practice) and specialization (gynecology, other oncology) using an allocation ratio of 1:1. After fulfilling the inclusion criteria and obtaining written informed consent from all participating physicians as well as, if necessary the heads of hospital departments, centers will be randomized by the study team. The randomization list will be generated by a statistician not otherwise involved in the study using SAS, version 9.4 (SAS Institute, Cary, NC, USA). The list will be transferred into a secured database (Microsoft Office Access 2010; Microsoft Corporation, Redmond, WA, USA) and be hidden behind the interface so that it will not be accessible to anyone involved in the random allocation or treatment. The order of randomization for both strata (gynecologist and oncologists) will follow the first-come first-served principle.

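### The model leaves out the randomised unit (centre), so paired department physicians are analysed as independent and intervals are somewhat too narrow if colleagues' outcomes are positively correlated

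*Protocol article*

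**What the plan says.** Allocation is by centre. Random allocation procedures: "The cluster-randomization into both groups will occur on a hospital department or private practice level". The same section gives one physician per practice and two per department, and describes the allocation as "stratified by type of center (hospital department or practice) and specialization (gynecology, other oncology) using an allocation ratio of 1:1". Physician recruitment and eligibility confirms the pairing: "From each hospital department two oncologists will have to be eligible and will be counted as a cluster". It also splits the 48 physicians equally between departments and practices.

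The analysis is by physician. Statistics: "Models will include the physician as a random (clustering) effect". Centre type and specialization are fixed effects, and the baseline value is a covariate where available. The section acknowledges that physicians are nested in clusters, then sets that level aside: "due to the small number of physicians per cluster (one to two), the cluster (center) will not be taken into the model". Adjusted means with 95% confidence intervals and exploratory P values will be reported. The sensitivity analysis described there adds baseline variables that differ between the groups. It does not add centre.

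**The concern.** In a cluster-randomised trial, the uncertainty of the treatment effect comes from variation between the randomised units. Two physicians from one department share patients, routines and a head of department who selects both, and they are always allocated together. Any similarity between them that the strata do not explain reduces the information in the pair. A physician-only model does not see this, because it fixes the centre variance at zero. The stratum effects do not help: they remove differences between types of centre, not differences between departments of the same type.

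Outcomes with one value per physician, such as the week 6 knowledge, expectation and attitude measures, are a special case. There the physician random effect cannot be separated from the residual. The model then has no working clustering term, and the same understatement applies.

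At stake is the width of the reported intervals, which readers of an exploratory trial rely on when planning further studies.

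**Working it through.** **Inputs from the article**
- 48 physicians, half from departments and half from practices (Physician recruitment and eligibility).
- Two physicians per department, one per practice, 1:1 allocation within strata (Random allocation procedures).
- 10 patients per physician (Abstract, Methods/design).
- Physician random effect, two stratum fixed effects, no centre (Statistics).

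**Assumption.** rho is the correlation between the mean outcomes (or single scores) of two colleagues in one department, after stratum adjustment. The article gives no value, so a range is shown.

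**1. The plan's own figure.** 48 × 10 = 480 patients, as stated. There is no power calculation to reproduce.

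**2. Randomised units.** 24 / 2 = 12 departments, plus 24 practices = 36 units, analysed as 48 physicians.

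**3. Variance.** With exact balance, each arm has 6 departments (12 physicians) and 12 practices (12 physicians). Let each physician mean have variance σ². The sum over an arm has variance 24σ² + 6 × 2·rho·σ², so

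Var(arm mean) = (σ²/24)(1 + rho/2).

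The physician-only model uses σ²/24. The ratio 1 + rho/2 is the same in both arms and so applies to the treatment difference.

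**4. Size.** True SE / model SE = √(1 + rho/2). The miss rate of a nominal 95% interval is 2·[1 − Φ(1.96/√(1 + rho/2))]. The simulation used 48 physician means in 36 centres, with specialization split evenly within each centre type, strata as fixed effects, 44 df (48 − 4) and 100,000 runs per rho. With balanced data, this equals the planned physician random-intercept model.

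| rho (assumed) | Variance factor | SE larger by, formula | SE larger by, simulated | Miss rate, formula | Miss rate, simulated |
|---|---|---|---|---|---|
| 0 | 1.00 | 0% | about 0% | 5.0% | 5.0% |
| 0.1 | 1.05 | 2.5% | 2.6% | 5.6% | 5.6% |
| 0.3 | 1.15 | 7.2% | 8.4% | 6.8% | 7.0% |
| 0.5 | 1.25 | 11.8% | 12.8% | 8.0% | 8.2% |

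The simulated values run slightly higher because the residual variance is itself a little underestimated when pairs are correlated. The mathematical limit, rho = 1, gives a factor of 1.5, an SE 22% larger and a miss rate of about 11% by the formula.

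**5. With centre in the analysis.** Using 32 df (36 − 4) and weights based on the true rho, the simulated error was 5.0–5.1%. With the centre variance estimated by REML and 32 df, it was about 4.4–5.4%. Both checks used physician means. The nested model on patient-level data and the logistic models were not simulated.

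**6. The stated reason.** A centre variance is estimated from the number of centres with at least two physicians, here 12, not from the number of physicians in each. Practices with one physician say nothing about the split between centre and physician, but they do not bias it. Twelve pairs are few: with REML on physician means (4,000 runs), the centre variance was estimated at exactly zero in about 40% of runs at rho 0.1, 27% at 0.2 and 17% at 0.3.

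**The case against.** The best defence is that little is lost. Half of the physicians are alone in their centre, so physician and centre coincide for them. The main source of clustering, about 10 patients per physician, is modelled. The trial is declared exploratory, with no formal sample size, no single primary outcome, no alpha and no decision rule, so a 5% rejection rate is not something it claims to control. With only 12 pairs, the centre variance will be imprecise and often estimated at zero. This gives the authors' worry about sparse clusters a practical basis.

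Most of this stands, and it limits the severity. It does not rescue the omission. Leaving centre out sets its variance to zero in every analysis, whereas the centre model does so only when the data suggest it, and that model kept the error near 5% in the simulations. The exploratory label does not correct a 95% interval.

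Three stronger readings are tempting, and the article does not support them:
- **The standard errors are certainly too small.** This holds only if residual within-department correlation is positive. That is plausible, but the article gives no figure.
- **The problem is much worse for hospital departments alone.** No hospital-only comparison is planned. Centre type enters only as a fixed effect.
- **A given patient-level intraclass correlation for centre fixes rho.** It does not. With 10 patients per physician, rho = τ²c / (τ²c + τ²p + σ²e/10), which also depends on the physician variance τ²p. With total variance 1, a centre share of 0.10 gives 0.10/(0.10 + 0 + 0.090) = 0.53 if colleagues do not differ at all, but 0.10/(0.10 + 0.05 + 0.085) = 0.43 with a physician share of 0.05. The article gives neither share.

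**Conclusion.** The point holds in conditional form. The planned model omits the unit that was randomised, and the reason given does not justify it. The variance of the treatment effect is understated by a factor of about 1 + rho/2. This is a modest shortfall for assumed rho between 0.1 and 0.5, and none if the centre variance is zero. The figures rest on exact balance, equal numbers of patients per physician and assumed values of rho.

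Severity is moderate. A reader might infer that the trial's results would be invalid without the change. The size of the effect and the exploratory status do not support that.

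**What to change.** Change the sentence in Statistics, and carry it into the SAP that the article promises before any data analysis. Suggested wording:

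*Models include centre (the unit of randomisation) as a random effect, with physician nested in centre where there are several observations per physician. For outcomes with one value per physician, centre is the only random effect. Degrees of freedom are by Kenward-Roger or Satterthwaite, or are based on the 36 centres (about 32). Centre is retained if the nested physician component is estimated at zero.*

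Because the centre variance will often be estimated at zero when rho is small, the SAP should also say which degrees of freedom then apply.

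The cost is one model statement and slightly wider intervals. If the centre variance is truly nil, the result is slightly conservative. Moving from 44 to 32 df alone raises the critical value from 2.015 to 2.037, and 2.037/2.015 = 1.011, so intervals widen by about 1%.

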### Qualitative data collection

A qualitative substudy will complement the quantitative findings. Qualitative semi-standardized telephone or online video interviews will be conducted with all oncology physicians of the control group who experienced both conditions (consultation with and without KOKON-KTO training). Interviews will occur 8 to 10 weeks after the on-site skills-training workshop of the control condition. The qualitative data will allow a fuller picture of the consultation experience.

Moreover, face-to-face-interviews will be conducted with all standardized patients after the on-site skills-training workshop. They will be interviewed in one-on-one, face-to-face, semi-structured interviews with one investigator to approach and explore patients’ perspective during KOKON-KTO consultations.

### Qualitative analysis

Control oncology physicians will be asked questions focusing on their personal experience when giving advice to their patients before and after the training. Standardized patients will be asked about their experience when getting advice from oncology physicians during the KOKON-KTO consultations. Transcripts will be imported into MAXQDA [25]. Data will be analyzed through content analysis according to Mayring and Flick [26, 27], deductive and inductive coding strategies will be combined. Deductive codes are predefined by the research team according to the semi-structured interview guideline. The coding of other subcategories of data analysis will follow a continuous process of extracting codes from conducted interviews and discussions among the team members. Patients’ quotes will be translated from German to English. Conducted interviews will be interpreted by two qualitative researchers in order to approximate reliability. Differences in the interpretation of the data will be discussed with the study team.

### Ethics

The study will be performed in agreement with the Declaration of Helsinki and has been approved by the relevant local ethics boards (Ethics Committee of Charité – Universitätsmedizin Berlin, Medical Association Hamburg, Medical Association Baden-Wuerttemberg, Medical Association Nord Rhine, Ethics Committee of the Medical Association of Westphalia-Lippe, Ethics Committee at the Medical Faculty of Würzburg, Ethics Committee of the Medical Faculty of Heidelberg, Ethics Commission of the Albert-Ludwigs-University of Freiburg). In addition, issues regarding data protection were approved by the local data protection officer at Charité – Universitätsmedizin Berlin. All study participants will provide oral and written informed consent.

Physicians will have to spend a considerable amount of time for the study including e-learning, workshop, assessment, and KOKON-KTO consultations. There is a risk that oncology physicians will feel overwhelmed by the training and study procedures. A user-centric approach will be used for the study documents and the KOKON-KTO blended learning. An experienced team will prepare the respective materials.

Standardized consultations in workshops or role plays can be perceived as stressful by some physicians and physicians in the control group may be burdened by the fact that they will only hand over a flyer with recommendation for reputable websites within a short consultation without a communication training. However, physicians in the control group will be prepared for this situation in a 45-min e-learning.

Patients will have to invest time for the study to complete questionnaires and there might be patients who will be tempted to use alternative strategies which interfere with their cancer treatment. To prevent these, patient assessments will be minimized. Moreover, physicians will be trained to inform about evidence-based CIM approaches and that CIM treatment, if used, should be complementary and not alternative to cancer treatments. Furthermore, they will mention, where applicable, the risks of interactions.

### Governance, quality assurance, and safety

This study is part of a larger network project (Competence Network Complementary Medicine in Oncology) that is managed by a steering group that consists of seven members. The principle investigator of this project is also a member of this steering group. Relevant design changes and safety issues as well as progress of the project according to predefined milestones will be discussed in the steering group that has monthly conference calls. Furthermore, the network project has an advisory board that can also provide advice for this trial.

The trial will be conducted according to the Standard Operating Procedures (SOPs) and the quality management protocol of the coordinating center (Institute for Social Medicine, Epidemiology, and Health Economics, certified according to DIN EN ISO 9001:2015). Data quality will be checked by a data manager following SOPs. The institute receives annual audits according to DIN EN ISO 9001:2015.

### Dissemination

We aim to publish the study results in international peer-reviewed medical journals. Moreover, we plan to present results nationally and internationally at oncology, gynecology, and CIM conferences and to provide website information.

## Discussion

This trial will help to determine the effects of a blended-learning training for a CIM consultation with cancer patients. We will evaluate outcomes at the physician-patient-interaction level. The study and the training that we aim to evaluate contain several unique aspects. First, this is a large cluster-randomized trial that will investigate a structured training on this topic for oncology physicians in Germany. Furthermore, the consultation about CIM in cancer care should not be longer that 20 min so it can be integrated into usual care. One of our previous studies demonstrated that oncology physicians found it difficult to integrate stand-alone time-intensive CIM consultations into their daily routine. However, physicians also stated that they found the additional time to talk with their patients satisfying [19]. Therefore, our concept will address this challenge. To overcome it, we will tailor the training to the needs of oncology physicians when giving advice to their own patients. This will make the consultation less time-consuming.

Another unique point is the broad investigation of effects on different levels. We will ask not only oncology physicians about their opinion on the training and the consultations but also the patients. Furthermore, we will analyze the physician-patient interaction as this was a major recommendation produced by our expert workshop on outcomes.

Our study protocol has several distinctive aspects including that cancer patients not only obtain their cancer care in hospital departments but also in private practices in Germany. We aim to include both types of institutions and will ask oncology physicians with varying specializations (oncology as well as gynecology) to participate in our study. Moreover, physicians from five different federal states will be asked to participate. In addition, we will include only CIM-inexperienced physicians in our study. Based on our previous pilot study we assume that they might gain a greater benefit from training on communicating with patients about CIM [18].

This study is subject to limitations. First, it should be mentioned that a 20-min consultation is not sufficient to cover all possible issues arising around CIM in oncology as well as other challenges that might occur during this consultation. The focus of this study is to train physicians for a more general approach that can be easily implemented in their daily medical work. For CIM consultations that are more complex and might have a different focus, existing guidelines and other settings can be applied [28].

Even though the consultations and the consultation manual were planned carefully and after consideration of expert opinions, it cannot be guaranteed that the discussion will be applicable to cancer patients in practice and under real-life conditions without restrictions. However, these doubts should be dispelled by the testing of the KOKON-KTO consultation manual by experienced oncology physicians who are unfamiliar with the training in advance. Furthermore, oncology physicians participating in the KOKON-KTO study will have exemplary consultations with standardized patients before conducting consultation with their own patients. The KOKON-KTO training will be the first to be tested in a randomized controlled trial with patients under real-life conditions.

There is a risk that oncology physicians in the control group may feel overwhelmed in the consultation situation due to the low level of CIM training. However, in routine care they frequently receive questions on CIM by their cancer patients. Being able to provide a leaflet might not solve the situation but perhaps improve it. The interviews and the completion of the interview assessments will take place during the working hours of the physicians. In the previous study, no aspects that we would have categorized as side effects of the consultations were documented. Future studies might think about appropriate safety measures for this type of interventions.

In addition, the study will not examine whether the physicians actually adhere to the manual and training and follow the recommendations when conducting their consultations. However, e-learning sections on indication-specific CIM therapies are intended to increase the knowledge about effectiveness and safety and, therefore, the quality of CIM advice in the KOKON-KTO consultations. Furthermore, the on-site skills-training workshop including a standardized patient setting will train the oncology physicians to adhere to the KOKON-KTO consultation manual. Neither physicians nor patients can be blinded regarding group allocation because of the different training content and consultation settings, and bias due to this cannot be excluded.

As another limitation of the study, the KOKON-KTO training, consisting of a 6-h e-learning and a 2-day on-site skills-training workshop, is relatively time-consuming and is, therefore, only suitable for physicians who are interested in the topic and in giving CIM advice to patients.

With regard to the measurement of the data, mainly self-administered questionnaires with inherent limitations will be applied. Moreover, the consultations conducted by the oncology physicians with standardized patients will not be recorded on video but merely assessed by a systematic external rating. This procedure results from our previous study [18], in which the participating oncology physicians were partially disapproving of video recordings. KOKON-KTO consultations will only be observed and objectively rated during the workshop at the end of the training. This study will not include radiation oncologists because of their different oncology setting. This way it is easier to develop the materials targeted to the treatment situation for our blended learning. For future trainings these materials might be added and evaluated.

In the case of questions regarding patient’s satisfaction with the consultation, ceiling effects may also occur, which have already occurred in our previous study [18]. Therefore, it might be important to get a better understanding of the meaning of satisfaction for this type of patients. However, since we will use outcomes on several levels we decided not to include a broader evaluation of satisfaction.

Our study will provide evidence on a training program (e-learning + workshop) for oncology physicians on advising their patients on CIM, and the study will offer data on the program’s effects in comparison to only handing out an information leaflet about reputable websites. Furthermore, the study will not only provide new information about the effects on outcomes at the physician level but also at the patient, and the patient-physician-interaction level.

